**Approved by the Ethical review committee of Mekran Medical College, Turbat, Pakistan**

**Letter ref.no. MMC/ERC/1/6/2024**

**Protocol date & Version: Date:1: 1st April 2024**

**Principal Investigator: [name] [name]**

**Co-investigator: [name] (Ph.D. Scholar)**

## Study Summary

| **Title** | **The Impact of Educational Intervention on Knowledge, Beliefs, and Practices of Breast Self-Examination among College Teachers: Protocol for a Cluster Randomized Control Trial** |
| --- | --- |
| **Background** | Breast cancer is a significant health concern, becoming more likely for women over time. Despite numerous studies on this topic among women in many countries, few have examined the importance of breast cancer screening among Pakistani females. This study aims to design, implement, and evaluate educational interventions for breast cancer prevention targeting female college professors in Pakistan. |
| **Primary objective** | To design, implement, and evaluate educational interventions for breast cancer prevention targeting female college professors in Pakistan. |
| **Methodology** | This study protocol is based on a single blind, parallel cluster randomized controlled trial (CRCT) design with an intervention time of 3 months. The clusters will be randomized into control and treatment groups, and baseline data from both groups will be acquired. A health belief theory-based breast self-examination intervention will be delivered to the intervention group, followed by the collection of post-intervention data at two different time points from both groups. The questionnaires will include basic questions on breast cancer symptoms, risk factors involved, detection methods, practices and frequency of performing breast self-examination, and beliefs about breast cancer. The control group will receive the intervention at the end of the study. |
| **Study Design** | Cluster randomized controlled trial (CRCT) |
| **Eligibility Criteria** | A. Inclusion criteria  For colleges  Willing to be a part of the study.  • For teachers  • Full-time faculty appointed in government colleges in Hyderabad district.  • Aged between 25-59 years.  • Willing to be part of the study.  B. Exclusion criteria  • For colleges  • Colleges that are not willing to participate in the study despite meeting the inclusion criteria.  • Colleges already participated in initial phases of study, pilot testing, and cross-sectional study.  • For Teachers  • Pregnant teachers and lactating mothers  • Those who are on sabbatical leave.  • Diagnosed/Recovered breast cancer patients.  • Teachers who will refuse to be part of the study |
| **Sample size** | 114 for both arms, 57 in each arm. |
| **Intervention** | Health belief theory-based breast self-examination intervention delivered to the intervention group |
| **Control Group** | Will receive the intervention at the end of the study |
| **Data Collection Points** | Baseline, post-intervention at two different time points, 1 month and 3 months. |
| **Primary Outcome** | Practice and frequency associated with breast self-examination |
| **Secondary Outcome** | Knowledge of breast cancer and breast self-examination, beliefs linked with breast cancer and breast self-examination |
| **Discussion** | This cluster randomized controlled trial aims to improve the efficacy and legitimacy of theory-based breast self-examination interventions by increasing women's knowledge of the need for breast cancer awareness and changing their attitudes to encourage early breast cancer detection. |

| Chief Investigator &Main supervisor | [name] [name] |
| --- | --- |
| Co-Investigator &Co-supervisor | [name] |
| Co-Investigator | [name] |

# Introduction

## 1.1 Rationale and Background of the study

Breast cancer ranks second globally among all cancers, with 1.7 million cases (11.9%), yet it ranks fifth in terms of mortality (522,000, 6.4%) due to its relatively favorable prognosis (Fahad Ullah, 2019) It is the most prevalent cancer in women worldwide, affecting both developed and underdeveloped regions, with higher incidences in less developed areas (883,000) compared to more developed ones (794,000)(Ramdas, Benn, & van Heerden, 2020). Pakistan stands among the top Asian countries in terms of breast cancer cases, affecting one in every nine women.

Breast health awareness is critical for early detection. Breast self-examination (BSE) is recommended monthly by the WHO to help women become familiar with their breast tissue and detect any changes early. However, BSE is significantly underutilized in Pakistan due to low awareness and knowledge about the technique(Javaeed, Rasheed, & Shafqat, 2021).This lack of awareness contributes to delayed diagnoses, with 89% of Pakistani patients diagnosed late, often at advanced stages(Saeed, Asim, & Sohail, 2021). Social and cultural attitudes towards breast cancer play a significant role in the delayed presentation, influenced by factors such as age, lack of awareness, and fear of treatment (Agha & Rind, 2021; Sobri et al., 2021).

While breast screening is crucial for detecting asymptomatic lumps early, the practice remains uncommon in Pakistan, further highlighting the need for increased awareness and education(Fitzgerald et al., 2022; Miller et al., 2020). Breast self-examination offers a straightforward method for women to monitor their breast health regularly and detect changes promptly(Oguta et al., 2022).

Despite the importance of BSE, many Pakistani women, including those in professions such as teaching, lack adequate knowledge and practice of this self-examination method (Shahani et al., 2020). Teaching is predominantly a female profession in Pakistan, with women comprising 60% of the 1.89 million teachers across private and public institutions(Government of pakistan 2022).Recognizing teachers as influential advocates for health behaviors among students, educational interventions targeting this group can effectively promote BSE and enhance breast health awareness at a societal level.

In conclusion, leveraging the role of teachers in promoting BSE among students and peers through targeted educational interventions is crucial. Such initiatives not only empower women with essential health knowledge but also contribute to improving early detection and reducing breast cancer mortality in Pakistan.

## 1.2 Research Objectives

To develop, validate, implement, and evaluate the effectiveness of a health educational intervention grounded on the health belief model in improving breast self-examination practices among college teachers.

**Specific Objectives**

1. To develop, validate, implement intervention, and evaluate the effectiveness of a health educational intervention in improving knowledge of breast cancer, knowledge, beliefs, and practices of breast self-examination.
2. To determine a significant association between the respondent’s characteristics, knowledge of breast cancer, knowledge, beliefs, and practices on breast self-examination among college teachers.
3. To determine the differences between and within the control, and intervention group, pre and post intervention on knowledge of breast cancer, knowledge, beliefs, and practice of breast self-examination at baseline, 1 month, and 3 months post interventions.

## 1.3 Theoretical framework based on Health belief model.

The HBM is centered on individuals' perceptions of their vulnerability to and seriousness of a disease, prompting them to take proactive steps to prevent it (Hayden, 2022).When individuals understand the risks and consequences of a disease and perceive themselves as susceptible, they are more likely to adopt preventive measures. Additionally, the model posits that individuals are inclined to engage in preventive practices if they believe that the benefits outweigh any psychological or financial costs associated with prevention (Ralph.J.Clemente, 2021).By targeting beliefs and attitudes, the HBM aims to interpret and predict health behaviors, guiding individuals toward adopting recommended medical advice and preventive measures(Almutari & Orji, 2021).

In essence, the HBM underscores the importance of individuals' perception of disease threat and consequences in influencing their health behaviors, thereby facilitating proactive health practices such as regular BSE for early detection of breast cancer(Htay et al., 2021).

**Fig** I Theoretical framework of the interrelation of HBM's concepts and relationship to behavior change. Source:(K. Glanz, Rimer, & Viswanath, 2008)

## 1.4 Application of Champion’s Health Belief Model on breast cancer screening

Evaluations of the BCS-related HBM constructs have been connected to both BSE and MMG behaviors (Champion, 1993, 1999). In the beginning, Champion created and approved scales for perceived susceptibility in 1984. BSE's perceived benefits, perceived advantages, and perceived barriers. Later,

in 1993, these assessments underwent adjustment, and a self-efficacy scale measure for BSE was introduced. The advantages and challenges of MMG were later updated(Champion, 1999).

The perception of benefits from BSE and MMG was used to address the advantages of screening behavior (BSE or MMG) to reduce the likelihood of death from BC. Finding a mass early, when BC can be treated, was one benefit. Barriers included modules like the anxiety of discovering a mass, the length of the exam, and the pain and radiation associated with the MMG test. Champion and colleagues also created a mammography-related self-efficacy scale. In which ten elements best describe a woman's confidence in her ability to follow the processes required to have an MMG screening(Champion, Skinner, & Menon, 2005).

The initial adaptation and validation of the Champion HBM scales for an African American population took place in 1997(Champion & Scott, 1997).Later, the Champion HBM scales were then tested among a variety of racial and ethnic groups and translated into several languages. Study participants included 100 first-generation Chinese American women(Wu & Yu, 2003), 656 from Turkey (Mikhail & Petro‐Nustas, 2001; Secginli & Nahcivan, 2004), 500 from Jordanian workers and students, and 264 females from south Korea. When the results of these investigations were combined, they validated the validity and reliability of translated HBM measures.

Since 1950, HBM has been one of the most often utilized conceptual frameworks in health behavior research to explain changes in health-related behaviors and serve as a basis for interventions. Intervention studies based on the HBM have revealed a significant improvement in BCS rates(Glanz, Rimer, & Viswanath, 2015) . Hence, the present study will consider the utility of the Champion HBM as a theoretical framework to understand Pakistani college teacher’s beliefs related to BC and to predict BCS.

## 1.5 Conceptual framework of study

Based on the literature review, this study conceptualized breast self-examination practice as a dependent variable. All independent variables, Individual factors (Sociodemographic & family history of breast cancer) and educational intervention, dependent variables which have effects on breast self-examination variable, that have been investigated in this study are demonstrated in Figure II.

Figure II: Conceptual framework of study

# Methodology

## 2.1 Study Location

The study will be conducted in Hyderabad district, located in the Sindh province of Southeast Pakistan. Hyderabad, positioned 175 kilometers north of Karachi, ranks as the second-largest city in Sindh and the eighth largest in Pakistan, with a population of 1,732,693 as per the 2017 census (Statistics, 2017). It serves as a significant hub connecting Greater Sindh with rural areas.

Ten colleges from Hyderabad District, with 686 teachers, are included. These colleges offer intermediate and degree programs. Their programs are in three main areas: Arts, Science, and Business (Commerce). The teachers at these colleges are very well educated. Most of them have master’s degrees in their subjects, and some even have PhDs. The minimum criteria for appointment are a master’s degree in the respective field. We will conduct several preliminary steps before starting the main study, a Cluster Randomized control trial. These include a pilot study and a pretest to make sure our research tools are accurate and effective. Additionally, a cross-sectional study will be carried out to gather initial data from the same group of people who will participate in the main study.

To ensure fairness, the ten colleges will be randomly divided into different groups. Each group will participate in a specific phase of the study. This random assignment helps to prevent bias and makes the results more reliable. Among these ten, six colleges are randomly selected for the Pilot & pretesting phase and the cross-sectional phase, leaving four colleges to include in the main study.

**Study Design:**

A single blinded, cluster randomized controlled trial (cRCT) will be carried out among female college teachers from government colleges in Hyderabad district. Colleges will serve as randomization units (clusters). The study will proceed through three phases:

**Baseline Data Collection:** Data will be collected from both control and intervention groups.

**Intervention Delivery**: The intervention will be administered to the intervention group during this phase.

**Follow-up Data Collection**: Follow-up data will be collected at two different post-intervention points: one month and three months later. The same questionnaire will be used for both control and intervention groups. The intervention module will be applied to the control group after the study's completion.

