## 2.8 Study outcomes

**2.8.1 Primary outcome**

The primary outcome for this study is the practice of Breast Self-Examination (BSE). This will be assessed based on the percentage of participants who consistently and effectively perform breast self-examinations. Participants will self-report on their BSE practices using a structured questionnaire. Regular BSE practice will be defined as performing the examination once a month, while any other response indicating irregular BSE will be categorized as non-practicing.

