**Reliability**

The reliability of our measurement instrument will be assured through various strategies tailored to the study's context and informed by previous research. Specifically, for items designed to measure attitudes, we will assess reliability using Cronbach's alpha, with a threshold set at 0.70 or higher to ensure internal consistency. Corrections will be made based on test outcomes to enhance reliability. Furthermore, employing consistent data collectors who will assess research participants both at baseline and during follow-up will add an extra layer of assurance regarding the instrument's reliability.

The questionnaire to be utilized in this cluster randomized controlled trial (cRCT) will be a validated and reliable tool, rigorously tested for validity and reliability by the study researchers before its deployment.

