## 2.11 Data collection

With the help of college coordinators, small meeting groups will be arranged in colleges. All the selected participants will be informed about the purpose and procedures of breast cancer awareness and BSE practices educational intervention trial by the researcher as well as the selection criteria will be explained.

After reading through the contents of the respondent information sheet, all participants who willingly show consent to be part of the study will be given a consent form to sign. Afterward, they will be requested to fill out a structured pre-tested baseline breast cancer knowledge, beliefs, and practice questionnaire in the English language. 1 month and 3 months post intervention, the same questionnaire will be administered to the intervention group and the control group respectively.

The same strategy will be followed in the control colleges, teachers will be selected randomly, but the purpose and procedure about the intervention will not be discussed, only the data collection procedure will be discussed with them. After getting written consent from them, they will be requested to fill in the questionnaire at the baseline, 1-month post-intervention (intervention delivered to intervention group), and three months post-intervention.

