## 2.12 Delivery of intervention module and participation

1. **Knowledge-based awareness session.**

After the collection of baseline data, a 60-minute one-day session of the educational program on breast cancer awareness and screening will be delivered to each intervention college by the study researcher with a group of 20 to 25 participants. Before implementing the intervention, researchers will ensure that all the participants must have a mobile phone to receive the reminder SMS and to watch the BSE video clip. The procedure description will be as follows,

One hour presentation along with a short video of 5 minutes duration about BSE performance will be presented, which will consist of general structure as well as functioning of normal breast, awareness on breast health, basic knowledge on breast cancer, and education on various screening methods will be provided by the researcher.

1. **Skill based training session.**

Followed by the training session, in which a breast model made up of silicon having multiple lumps on it will be used for demonstration of BSE method, during this section, participants will learn the palpation technique, the search strategy, and signs of BC that are important for respondents to know. Later, the participants will be asked to perform BSE on the model and look for abnormalities.

1. **Take home messages for participants.**

A leaflet with the same information that was provided in the session will be given to every participant when the educational session ends.

A short film about BSE performance will be sent to the participants via WhatsApp, and a BC logo wall hanging will also be provided to be hung in the participants ‘room. Such materials will be believed to remind participants about BCS practice and monthly BSE performance. A short WhatsApp reminder message will be sent to all participants of the intervention group for the period of three months.

1. **Souvenirs as a reminder for breast self-examination**

Some souvenirs will be given to the participants, like a key chain, a writing pen, and a note pad with the breast cancer logo and a message “**know your risk**” get screening timely! To remind them of breast self-examination.

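### The trial is called single-blind without saying who is blinded, and its self-reported primary outcome is open to over-reporting by intervention teachers who know they were trained

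*Combined protocol and SAP*

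**What the plan says.** The Study Summary (Methodology row) states: "This study protocol is based on a single blind, parallel cluster randomized controlled trial (CRCT) design". The Study Design section repeats the label: "A single blinded, cluster randomized controlled trial (cRCT) will be carried out among female college teachers". Neither place says who is blinded, by what means, or whether blinding is checked.

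Section 2.11 treats the arms differently. In the intervention colleges teachers are "informed about the purpose and procedures of breast cancer awareness and BSE practices educational intervention trial by the researcher". In the control colleges the intervention is not discussed and only data collection is explained. Under section 2.12 the study researcher delivers the session. Intervention teachers practise on a breast model and receive a leaflet, a film, a wall hanging and three months of WhatsApp reminders. They also get small gifts: "Some souvenirs will be given to the participants, like a key chain, a writing pen, and a note pad with the breast cancer logo". Controls receive the material after the last follow-up.

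On measurement, section 2.8.1 says: "Participants will self-report on their BSE practices using a structured questionnaire". Section 2.9 makes the questionnaire self-administered. Section IV of the questionnaire records practice with two tick-box items. The Reliability text in section 2.10 plans on "employing consistent data collectors who will assess research participants both at baseline and during follow-up" and does not mention allocation. The Data Summarizing and Analysis section does not say whether the analyst is masked.

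**The concern.** A reader takes a single-blind label to mean that someone who could bias the result does not know the allocation. Here the person who produces the primary outcome is the teacher filling in the form. In the intervention arm she knows she was trained, and the response that counts as success is the monthly behaviour that her reminders and souvenirs promote. A control teacher has no comparable reason to choose it. No objective check of practice is planned.

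Any gap between the arms in over-reporting enters the estimated effect and cannot be separated afterwards from real behaviour change. The unqualified label implies protection against this, and the written procedures do not provide it in the arm where over-reporting is most likely.

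**Working it through.** **Who could be blind, by role**

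- Intervention teachers: no. They are told about the intervention trial (2.11), then trained and reminded (2.12).
- Trainer: no. The study researcher delivers the session (2.12).
- Control teachers: partly. The intervention is not discussed with them (2.11).
- Data collectors: not stated. The Reliability text says only that they stay the same over time. Whoever gives the briefing in 2.11 must know the arm, because its content differs by arm, but the plan does not say that this person is a data collector.
- Analyst: not stated.
- Outcome assessor: the teacher herself (2.8.1, 2.9), so unblinded in the intervention arm.

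**The plan's own figures**

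The plan gives no figure for blinding or reporting bias. Its sample size follows from its stated 14 per group: 28 × 2.96 = 82.88, taken as 83; 83/0.8 = 103.75, taken as 103; 103/0.9 = 114.4, taken as 114. That total is not in question here. Two Appendix II inputs are used below: 26% regular practice in controls and 85.6% in the intervention group, a planned difference of 85.6 − 26 = 59.6 points.

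**Size of a possible bias**

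Let T be the true intervention rate, C the true control rate, and q the share of intervention non-practisers who report monthly examination. Assume no over-reporting in controls.

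Apparent difference = (T − C) + (1 − T) × q, so the excess is (1 − T) × q.

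The documents give no value for q. Values of 10% to 30% are assumed.

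| q | No true effect (T = 26%): 0.74 × q | True rate as planned (T = 85.6%): 0.144 × q |
| --- | --- | --- |
| 10% | 7.4 points | 1.4 points |
| 20% | 14.8 points | 2.9 points |
| 30% | 22.2 points | 4.3 points |

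For reporting bias alone to produce the planned difference, q would have to be 0.596/0.74, about 81%.

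**Chance of a falsely significant result at q = 30% with no true effect**

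The reported rates would be 48.2% and 26%, tested two-sided at 5%.

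- With 57 per arm and the plan's design effect of 2.96, the effective number is 57/2.96 = 19.3 per arm and the chance is about 29%.
- With the sampled cluster size 114/4 = 28.5, the design effect is 1 + 27.5 × 0.02 = 1.55, the effective number is 36.8 and the chance is about 50%.
- With 57 × 0.9 × 0.8 = 41 completers per arm, the two chances are about 22% and 38%.

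These are normal approximations that ignore the small number of colleges (two per arm), so they show order of magnitude only.

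**The case against.** The best defence is that section 2.11 does keep control teachers uninformed of the intervention, and this may be what the label means. That stands as a fact about control teachers, so it would be wrong to say that all teachers are unblinded. The plan never says that this is the intended meaning. If it is, the masked arm is the one with little reason to over-report, and expectation remains unequal between arms.

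A reader might also infer that the data collectors are unblinded, because whole colleges are allocated and branded items are handed out. The documents do not support that as a stated procedure. They are silent on what collectors know, and the wall hanging's location is given only as the participants' room, which may not be at the college. With a self-administered form, collector knowledge also matters less than the teacher's own.

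A reader might further infer that follow-up forms are completed in group meetings with the trainer present. Section 2.11 describes small groups for briefing, consent and the baseline form, and gives no setting for the 1- and 3-month forms. That is a gap, not a stated practice.

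Unblinded recipients are inherent in an educational intervention, and the over-reporting rates above are assumed. Both objections stand. They limit the severity and the precision of the point without restoring the label. The consent and information pages and the flow diagram were not available for this review, so a blinding statement there cannot be excluded.

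**Conclusion.** The point holds in a limited form. The single-blind label is unsupported: no blinded party is named, intervention teachers and the trainer cannot be blind, control teachers are only kept uninformed, and the status of collectors and analyst is not given. The self-reported primary outcome is therefore open to differential over-reporting in the intervention arm.

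The size is unknown. The 7.4 to 22.2 points rest on three assumptions: no true effect, a 26% true rate in both arms, and over-reporting of 10% to 30% in the intervention arm only. If control teachers also over-report, the excess is smaller, and at the planned true rate it is at most 4.3 points over the same range. A reader might infer that such bias could account for the whole planned effect. That would need about 81% over-reporting, and nothing in the documents suggests so high a rate. Bias of this kind could create or inflate a modest positive result.

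This should be fixed before the first follow-up forms go out. It does not affect the sample size or the choice of primary test.

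**What to change.** 1. In the Study Summary and Study Design, replace the unqualified label with a statement that intervention teachers and the trainer are not blinded and that control teachers are only kept uninformed of the intervention. Say also whether collectors and the analyst know the allocation.
2. State that the primary conclusion will be an effect on self-reported practice of breast self-examination by unblinded participants.
3. In section 2.11, require that the 1- and 3-month forms in all four colleges carry a study code only, are completed individually, and are returned sealed without the person who delivered the session present. The data collectors or college coordinators already planned can hand them out. The code should link each teacher's forms across time points.
4. In the Data Summarizing and Analysis section, the arms can be coded X and Y until the analysis is final. This helps only if the analyst is not the trainer, and the plan does not name the analyst.

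The cost is protocol wording, code numbers, envelopes and the loss of the unqualified single-blind label. Steps 3 and 4 reduce the pressure to give the expected answer but do not make intervention teachers blind, so step 2 is needed in any case. Step 3 cannot be added after follow-up has been collected.
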